##### Analysis of the mediating effect of psychosocial variables

Mediation analyses are an important step in evaluation of theory-based interventions as they help to determine the extent to which behavioral change during the intervention is explained by changes in the variables included in the underlying theoretical model [24]. To test whether the effect of the GLMC on children’s PA levels is mediated by the variables specified in the underlying theoretical model (Fig. 3) we will perform sequential mediation analyses using the SPSS (version 21) macro PROCESS, with 10,000 bootstrapped replications [59]. PROCESS allows one to conduct multiple mediator analysis in linear multiple regression models whilst accounting for covariates (e.g.*,* age, sex, PA level at T0). The independent variable of the model will be the group, (coded 1 for the intervention group and 0 for the control group). The dependent variable will be PA level at T3. The multiple mediation analyses will include 3 sequences of mediators (see [60, 61] for a similar approach). Change in parental shared family PA and parental social support for PA between T0 and T3 will constitute the first sequence of mediators, change in children’s attitudes, subjective norms and perceived behavioral control between T0 and T3 will constitute the second sequence of mediators, and change in children’s intentions, perception of activity opportunities and planning between T0 and T3 will constitute the third sequence of mediators. In addition, moderation analyses will be conducted to test whether the effects of change in intentions on the level of PA of children is moderated by different levels of perceptions of activity opportunities and different levels of planning (see Fig. 3). The results of analyses will be presented using two types of coefficients: a regression coefficient (*β*) for each parameter and an indirect effect coefficient (*θ*) for each indirect pathway (via a specific mediator) between the independent variable (group) and the dependent variable (PA at T3). All the statistical tests will be two-sided and *p*s < 0.05 will be considered significant.

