### Study design and population

All the year 3 and year 4 children attending primary schools in the Hérault, Gard, and Aude departments of France (and their parents) are eligible to participate in the study. There is wide variation in the sociodemographic background and PA levels of children attending schools in these departments. The intervention involves children and their parents, and is implemented by multiple local, grass-roots partners, namely, school teachers, municipal officials and policy stakeholders from community agencies and district councils. To avoid contamination between the intervention and control groups randomization will be done at community of communes level (a community of communes is an administrative grouping of several cities or villages), thus all the schools in a given community of communes will represent a cluster.

The study is a two-armed prospective cluster-randomized, controlled intervention trial. Communities of communes will be randomized in equal proportions to one of the two study arms: 1) the GLMC experimental arm, which will receive a 24-month (6 weeks per year) multilevel, extended TPB-based program intended to promote PA; 2) the control arm, which will not receive any intervention (Fig. 1).

After randomization, schools belonging to the communities of communes and their teachers will be informed about the study and their arm allocation by a research assistant. A member of staff outside the research team will introduce data into the computer in separate datasheets so that the researchers can analyze data without having access to information about the allocation. Eligible children from schools and classes willing to participate in the study, and their parents, will receive a written note explaining the research goal, design, assessment protocol (including information about the wearing of accelerometers) and intervention content (see flow diagram of schedule in Fig. 2). Children with medical conditions or and children taking medication that would limit their physical activity will not be included. Children will be given consent forms to take home for their parents to sign. There are three independent consent forms providing: *(i)* consent to the child filling in questionnaires; *(ii)* consent to fill in the parental questionnaires; *(iii)* consent to the child wearing an accelerometer.

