##### Feasibility studies

Two preliminary pilot studies were conducted to confirm that it is feasible to deliver the GLMC intervention and evaluate the participating children and parents. These studies also represented an opportunity to assess the strengths and weaknesses of the intervention.

The first pilot study was carried out in and involved 306 children aged 7 to 11 years old attending 6 public schools and 104 of their parents. During this study we noted that children found the concept of ‘energy cubes’ very attractive; in fact they became something of a fad. We also found that the format of parents’ meetings (see Module 5, Table 1) were more attractive when they were held at the children’s schools rather than in town halls and organized as ‘round-table discussions about promoting PA’ with teachers, municipal officials and local policy stakeholders rather than organized as ‘PA promotion presentations’.

In 2015 a second study involving 793 children aged 7 to 11 years old from 16 public schools and 329 of their parents was carried out. This pilot study was used to test the feasibility of the evaluation procedure and the potential for recruitment. We found that it was feasible to administer the children’s questionnaires (evaluating self-reported PA, TPB variables and additional psychosocial variables) in a classroom setting (i.e.*,* 50–55 min for the completion of the questionnaire for a class of 20–25 children). We also confirmed the feasibility of the procedure for distributing and retrieving accelerometers from a subsample of children. The parents’ questionnaire was also reported to be feasible. Sixteen of the 53 schools (30%) that were contacted agreed to participate and the rates of return of signed consent forms were 86.7% for the child’s participation in the study, 37% for the wearing of an accelerometer by the child and 33.6% for completion of the parents’ questionnaire.

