### Statistical considerations

#### Power analysis

Without considering the clustering effect, it is calculated that 180 children per randomization group are needed to observe a 15% difference in the proportions of children in the intervention and control groups achieving the current internationally recommended level of PA with 80% power, given a two-tailed type I error rate of 5%. We assumed that 35% of children would be achieving the current internationally recommended PA level of 60 min of moderate to vigorous PA per day at baseline.

The clustering structure of the randomization requires a variation inflation factor equal to *1 + (m(1 + cv*^*2*^*)-1)r* [58] where *m* is the mean number of children per cluster; *cv* is a coefficient of variation equal to ratio of the standard deviation of the cluster sizes and *m*; *r* is the intraclass correlation coefficient (ICC) for the communes of one community of communes (i.e.*,* one cluster) and reflects the degree of cluster homogeneity. *r* was set at 0.005 based on preliminary data obtained from pilot studies and the database of ICCs [56] .

Given the number of children in selected community of communes clusters (*m* = 781 children on average; *cv* = 1.05), 3400 subjects are required to observe a 15% difference in the proportion of each group reaching the current international recommendation of 60 min with 80% power. Assuming a loss-to-follow-up rate of 15%, a reasonable estimate of the required sample size is 4000 subjects, i.e.*,* 2000 in the intervention group and 2000 in the control group, corresponding to around 160 classes.

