##### Effectiveness analysis

Baseline similarity of the intervention and control groups will be assessed at cluster level (i.e.*,* communities of communes) and child level using descriptive statistics and *T*-tests or Mann-Whitney tests for continuous variables and χ^2^ or Fisher’s exact tests for categorical variables.

Linear mixed models will be used to determine the impact of the intervention impact; this will allow us to calculate fixed effects, such as the effect of randomization group, and random effects such as the effect of subjects and clusters given the potential for intraclass correlations (between and within subjects and clusters). Longitudinal analysis of the dichotomous primary endpoint (i.e.*,* achieving or not achieving the current internationally recommended PA level of 60 min of moderate to vigorous PA per day) will be conducted with a logit link function, effects of subject, group, time and cluster and the time*group interaction will be calculated. The effect of the intervention will be evaluated at child (and parent) level, but also at school, commune and community of communes levels. Potential confounders such as age and sex will be included in the model as covariates.

The same analytical approach will be applied to the secondary outcome variables. The effect of the intervention on TPB variables and other psychosocial continuous variables will be assessed using similar linear mixed models, with a regress link function.

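### The mediation analysis as specified leaves out the community clustering that the sample size and effectiveness models account for, so the precision of the group-to-mediator paths is overstated

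*Protocol article*

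**What the plan says.** The section on the mediating effect of psychosocial variables states: "we will perform sequential mediation analyses using the SPSS (version 21) macro PROCESS, with 10,000 bootstrapped replications". It describes the model class as follows: "PROCESS allows one to conduct multiple mediator analysis in linear multiple regression models whilst accounting for covariates". The example covariates are age, sex and baseline physical activity (PA). The exposure is randomised group coded 1/0, the outcome is PA at T3, and the mediators are T0-to-T3 changes in three successive sets: parental variables, then attitudes, norms and control, then intentions, opportunities and planning. A regression coefficient is reported for each parameter and an indirect-effect coefficient for each pathway, at two-sided 5%.

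On allocation, Study design and population says "thus all the schools in a given community of communes will represent a cluster". On its consequence, Power analysis says "The clustering structure of the randomization requires a variation inflation factor". Effectiveness analysis fits "random effects such as the effect of subjects and clusters given the potential for intraclass correlations", and adds: "The effect of the intervention on TPB variables and other psychosocial continuous variables will be assessed using similar linear mixed models".

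**The concern.** Group does not vary within a community, so its effect on any mediator is estimated from differences between communities. A regression that treats children as independent takes the precision of that estimate from the number of children. Chance differences between a few communities can then pass for an effect of the intervention on attitudes, norms or planning, and carry through to the indirect effects.

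This is not a detail left to a fuller document. The article names the tool, the model class, example covariates, the number of replications and the significance threshold, and what it names has no cluster component.

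Two things are at stake. The Discussion presents the test of the extended theory of planned behavior as a key contribution. And the same group effect on a child's psychosocial variable would be tested twice, once with clustering and once without, so the two reports could disagree.

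**Working it through.** **Inputs.** From Power analysis: 180 children per group before clustering, mean cluster size m = 781, cv = 1.05, ICC r = 0.005, 3400 children required, 15% loss, 4000 recruited. From Feasibility studies: 30% of schools agreed, and consent-return rates were 86.7% (child) and 33.6% (parent questionnaire). Assumed, because not given: the mediators' ICC (0.005, with 0.001 as a lower case), the number of communities (5 to 20) and the number of children analysed (3400 or about 1140).

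**The plan's own figure.** Design effect (DEFF) = 1 + (m(1 + cv²) − 1)r = 1 + (781 × 2.1025 − 1) × 0.005 = 9.21. Then 2 × 180 × 9.21 ≈ 3314, within 3% of the stated 3400, and 3400/0.85 = 4000. The plan therefore does rest on a design effect of about 9.2.

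**Number of communities.** If 781 children per community were enrolled, 4000/781 ≈ 5 communities. If 781 counts all eligible children and the pilot rates apply, 781 × 0.30 × 0.867 ≈ 203 per community, and 4000/203 ≈ 20. The article does not settle which, so both ends are carried.

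**Large-sample formula.** True rate of a nominal 5% test = 2(1 − Φ(1.96/√DEFF)). At DEFF 9.21, √DEFF = 3.03 and the rate is 52%. The formula overstates the error when there are few communities of very unequal size, so it was set against simulation: no true group effect, a normally distributed mediator, unequal cluster sizes, and a group comparison that ignores clustering.

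| Children | Communities | Mean size | DEFF at r = 0.005 | Formula | Simulation |
|---|---|---|---|---|---|
| 3400 | 5 | 680 | 8.14 | 49% | 36% |
| 3400 | 12 | 283 | 3.97 | 33% | 28% |
| 3400 | 20 | 170 | 2.78 | 24% | 22% |
| 1142 | 5 | 228 | 3.40 | 29% | 19% |
| 1142 | 12 | 95 | 2.00 | 17% | 13% |
| 1142 | 20 | 57 | 1.60 | 12% | 12% |

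At r = 0.001 the simulated rates run from about 6% to 13% over the same settings. A further run with 20,000 replicates per setting agreed with these figures to within about two percentage points. With 40 communities, 3400 children and r = 0.005, simulation gave about 15%.

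**Does the bootstrap help?** Not if it resamples children. In a separate simulation (400 runs per setting, r = 0.005, a real mediator-to-outcome effect and no group effect), a child-level bootstrap wrongly declared an indirect effect in 43% of runs with 4 equal clusters of 850, and in 28% and 23% with 10 and 20 unequal clusters and 3400 children. The unclustered tests of the group path erred in 41%, 26% and 20%.

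**The 1142.** This is 3400 × 0.336. It applies only if the sequential model is fitted to children with parent data, and only if 33.6% is the right share of children already enrolled. Relative to consented children the share could be 0.336/0.867 = 38.8% (about 1318). From the pilot's 329 parents for 793 children it is 41.5% (about 1411).

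**The case against.** **The size is not known.** The ICC of 0.005 was set in the power calculation for the PA outcome, and no value is given for change in the mediators. The number of communities is not stated, and five would be fewer than the six department-by-environment strata. This stands. A reader might apply the design effect of 9.2 directly and conclude that error rates reach 50% or more. The documents do not support that: 52% comes only from a large-sample formula with 781 analysed children per community, and simulation with 5 communities gives about 36%.

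**A smaller analysed sample reduces the problem.** If missing parent data leave about 1140 children, clusters shrink and the inflation falls to 12–19%. This stands, and the two problems must not be added together. A reader might also infer that two thirds of children will be discarded. The article does not specify complete-case fitting for this analysis, it plans a missing-data sensitivity analysis, and the 33.6% is a consent-return rate from a pilot.

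**The resampling unit is not stated.** This is true. Child-level resampling is an inference; nothing in the section points to resampling of communities.

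**The harm is limited.** Mediation is neither the primary objective nor a listed secondary one. Group effects on the children's psychosocial variables are tested separately with cluster effects. Mediator-to-PA paths vary between children and are not inflated in the same way, and a false indirect effect also needs a non-null mediator-to-PA path. All of this stands and confines the point to the mediation results. It does not remove the inconsistency: the section still reports a tested coefficient for each group path, from a model that leaves out the clustering.

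**Conclusion.** The point holds in limited form. The mediation analysis as written is inconsistent with the trial's design, sample size and effectiveness models. It understates the standard errors of the group-to-mediator paths and, through them, the width of the indirect-effect intervals.

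Under an ICC of 0.005 and a cv of 1.05, a nominal 5% test of a group path has a true rate of about 22–36% with 3400 children in 20 to 5 communities, or about 12–19% with roughly 1140. At an ICC of 0.001 it is about 6–13%; an ICC above 0.005 would raise the rates. All of these are conditional on values the article does not give for this analysis.

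It would go too far to say that every path is affected to the same degree, or that the primary result is compromised. The change should be made before analysis.

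**What to change.** Account for the community of communes in every mediation equation. The form that matches the effectiveness models is a random community effect, with the group paths tested on small-sample, cluster-based degrees of freedom. Build the indirect-effect intervals from those cluster-adjusted estimates, for example Monte Carlo distribution-of-product intervals, instead of an individual-level bootstrap. State the number of communities and report the estimated ICC of each mediator, so that readers can judge the remaining uncertainty.

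The cost is a different software routine, some analyst time and wider intervals, which will be very wide if there are only about five communities. No new data are needed.

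Optionally, report the child-variable chain on all children alongside the prespecified chain that includes the parental mediators, given the 33.6% parent-questionnaire consent in the pilot. This should sit beside the prespecified chain, not replace it: the parental variables belong to the trial's theoretical model, and demoting them is a trade-off for the investigators to weigh.

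### The mediation analysis is fixed as single-level regression although communities were randomised, so false mediation would be declared in roughly 8–40% of trials instead of 5%, depending on the number of communities and complete parent data

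*Protocol article*

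**What the plan says.** Under *Study design and population*, the unit of randomisation is the community of communes: "thus all the schools in a given community of communes will represent a cluster". Under *Power analysis*, the article accepts the statistical consequence: "The clustering structure of the randomization requires a variation inflation factor equal to" a formula in the mean cluster size, its coefficient of variation and the ICC. Under *Effectiveness analysis*, the mixed models carry "random effects such as the effect of subjects and clusters given the potential for intraclass correlations", and similar mixed models are specified for the theory-of-planned-behaviour and other continuous psychosocial variables.

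Under *Analysis of the mediating effect of psychosocial variables*, the method changes. The analysis uses the "macro PROCESS, with 10,000 bootstrapped replications". The model class is given as "PROCESS allows one to conduct multiple mediator analysis in linear multiple regression models whilst accounting for covariates", with age, sex and baseline activity as examples of covariates. On the exposure the article says: "The independent variable of the model will be the group, (coded 1 for the intervention group and 0 for the control group". The outcome is physical activity at T3. The mediators are T0-to-T3 changes in three sequences: parental variables first, then attitudes, norms and perceived control, then intentions, opportunities and planning. Tests are two-sided at 0.05. The section mentions no community random effect, no cluster-robust standard error and no resampling of communities.

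**The concern.** Group varies only between communities, so the information on any effect of group is limited by the number of communities as well as the number of children. Ordinary regression on children ignores the between-community variation and understates the standard error of each path that starts at group. A bootstrap that draws children one by one repeats the error, because it never varies which communities were sampled. Adding community indicators as covariates would not help, since group is constant within a community and could not then be estimated.

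The article would thus analyse the same variables in two incompatible ways. The clustered model could find no clear effect of the programme on attitudes, while the mediation model reports a significant pathway through attitudes. The *Discussion* presents the psychosocial mechanism as one of the trial's contributions, so a false pathway would be read as support for the extended theory.

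**Working it through.** **Inputs.** From *Power analysis*: mean cluster size m = 781, cv = 1.05, ICC r = 0.005, 180 children per arm before clustering, 3400 after it, 4000 after 15% loss. From *Feasibility studies*: consent-form return of 86.7% for the child and 33.6% for the parents' questionnaire. The article does not give the number of communities or the ICC of the mediator change scores, so both are assumed below.

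**Step 1: the plan's own figure.** The variance inflation factor (VIF) is 1 + (m(1 + cv²) − 1)r = 1 + (781 × 2.1025 − 1) × 0.005 = 9.205. Then 2 × 180 × 9.205 = 3314, within 3% of the stated 3400, and 3400 / 0.85 = 4000. The planning assumptions are therefore reproduced closely.

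**Step 2: what that factor does to an unclustered test.** The standard error is too small by √9.205 = 3.03. The actual error of a nominal 5% test of group is P(|Z| > 1.96 / 3.03) = 0.518, about 52%. This formula value needs about 781 *analysed* children per community. With 3400 children that is 3400 / 781 = 4.4 communities.

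**Step 3: the same formula for other numbers of communities** (3400 analysed, ICC 0.005, cv 1.05):

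| Communities | Children per community | VIF | Formula error |
|---|---|---|---|
| 10 | 340 | 4.57 | 36% |
| 20 | 170 | 2.78 | 24% |
| 40 | 85 | 1.89 | 15% |
| 60 | 57 | 1.59 | 12% |

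With 20 communities, an ICC from 0.001 to 0.02 moves the figure from 9% to 49%.

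**Step 4: how many children are analysed.** The first sequence of mediators comes from parents. If complete parent data are required (an assumption), the sample falls to about 3400 × 33.6 / 86.7 = 1318.

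**Step 5: the indirect effect by simulation.** Set-up: no effect of group on the mediator, a real mediator-to-activity link, ICC 0.005, cv 1.05, ordinary regression. A product-of-paths interval stands in for the child-level bootstrap. Share of trials in which mediation is falsely declared:

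| Communities | 3400 children | about 1318 children |
|---|---|---|
| 4 | 38–43% | 25% |
| 10 | 27–30% | 17% |
| 20 | 19–22% | 11–14% |
| 40 | 14–16% | 8–9% |

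Where a range is shown, repeated simulations differed by that much. With few communities the simulated rates lie below the formula values; at 40 communities and 3400 children the two agree.

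**Step 6: boundary checks.** With an ICC of zero (20 communities, 3400 children, real mediator-to-activity link) the false-mediation rate is 5–7%, so the excess comes from clustering. If the mediator does not predict activity either, the rate is about 2% or less.

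The simulations used a single mediator. Neither the three-sequence chain nor the direct effect was simulated. For the direct effect the argument is the same as for the group-to-mediator paths, but its size depends on the clustering of activity given the mediators, which is not stated.

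**The case against.** The fairest defence is that this is an article, that a full analysis plan may add a cluster adjustment, and that mediation is listed under neither the primary nor the secondary objectives. The second part stands and limits the weight of the point. The first does not: the article commits to a macro, a model class, a bootstrap count, an exposure, an outcome, a mediator order and a significance level. That is a method chosen, and it conflicts with the article's own treatment of clustering.

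A second defence is that the size is unknown, because the article states neither the number of communities nor the mediators' ICC, and the ICC of 0.005 was set for the sample size rather than for change scores. This stands, and it is why only a range is given. With many small communities or a very small ICC the error approaches 5%.

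Three stronger readings should be resisted:

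- **A 52% error rate.** A reader might take this straight from the VIF of 9.2. It presumes about 781 analysed children in each of four or five communities, and even with four communities the simulated rate is about 38–43%.
- **The moderation analyses fail too.** The article says "moderation analyses will be conducted to test whether the effects of change in intentions on the level of PA of children is moderated" by opportunities and planning, but names neither PROCESS nor any model for this. The interaction is between child-level variables, and its simulated error was about 4–6%.
- **The trial's main result is at risk.** The primary and secondary effectiveness analyses use models with cluster effects and are not touched by this point.

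**Conclusion.** The point holds for the group-to-mediator paths and the direct effect, and for the indirect effects when the mediator truly predicts activity, as the trial's theory presumes. Assuming ICC 0.005 and cv 1.05, false mediation would be declared in roughly 15–40% of trials with 3400 analysed children and 40 down to 4 communities. If incomplete parent data leave about 1300 children, it would be roughly 8–25%. The intended rate is 5%. The direction of the error is certain for any positive ICC; its size rests on the assumed ICC, number of communities and analysed sample. The analysis explains mechanism and does not decide effectiveness, so this should be fixed but does not endanger the trial's main conclusion.

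**What to change.** Keep the path structure, mediator sequences and covariates, and replace the single-level estimation. Fit each path in a model with a community random intercept, with the group-to-mediator paths consistent with the mixed models already specified under *Effectiveness analysis*. Build the indirect-effect intervals from the clustered standard errors, for example by simulating the product of the paths, using small-sample degrees of freedom tied to the number of communities. Do not bootstrap children as independent units. State the number of communities and report the observed ICC of each mediator change score.

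The small-sample correction is essential. A random intercept with normal-theory tests still gave errors of 17%, 11.5% and 7.5% for the group effect with 4, 6 and 10 communities (3400 children, ICC 0.005), so adding the intercept alone would not restore 5% where the problem is worst.

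The cost is analysis wording, some code outside PROCESS, and wider intervals for the indirect effects. No change to design, recruitment or data collection is needed.

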### Intervention

#### Rationale and theoretical framework: applying and extending the TPB model

The GLMC is a multilevel intervention carried out in school, family and community settings. The multilevel framework targets both personal and environmental factors that are important to behavioral change [25], particularly in children [26]. The TPB model appears a particularly suitable foundation for the GLMC intervention as it includes intrapersonal (e.g.*,* attitudes) and environmental variables (e.g.*,* subjective norms) [21]. According to Ajzen [21], intentions are the proximal determinant of behavior and reflect one’s motivation to perform a given behavior. Intentions are determined by three factors: attitudes, subjective norms and perceived behavioral control. Attitudes can be defined as the overall positive or negative evaluation of the target behavior and has both an affective (e.g.*,* enjoyable vs. unenjoyable) and an instrumental (e.g.*,* beneficial vs. harmful) component. Subjective norms also consist of two related components: a descriptive norm is an individual’s perception of how often important others (e.g.*,* friends, siblings) display a given behavior; whereas an injunctive norm represents an individual’s perception of how much others want him/her to perform a given behavior. Finally, perceived behavioral control is one’s perception of one’s ability to perform a given behavior in line with intentions. It is hypothesized that perceived behavioral control directly predicts performance of the relevant behavior (Fig. 3).

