##### Psychosocial variables

The psychosocial variables to be measured are the TPB variables (i.e.*,* attitudes, subjective norms, perceived behavioral control and intentions) and the variables added to the theoretical model underlying the GLMC to fill the intentions-behavior gap (i.e.*,* planning, perception of activity opportunities) (Fig. 3). All 30 questionnaire items have been tested in feasibility studies (details of feasibility testing are given below). Responses to all items are given using a four-point scale: 1 (strongly disagree); 2 (disagree); 3 (agree); 4 (strongly agree).

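### The mediation model relates T3 activity to raw T0–T3 changes and names no mediator's own T0 score as a covariate; if those scores are left out, mediator-to-activity paths are likely attenuated when activity follows the T3 level

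*Protocol article*

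**What the plan says.** All of this is in the Protocol article, section on the mediating effect of psychosocial variables, unless another section is named.

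- Outcome: "The dependent variable will be PA level at T3". This is a level, not a change.
- Exposure: randomised group, "coded 1 for the intervention group and 0 for the control group".
- Mediators, eight in three sequences (2 + 3 + 3), all raw T0–T3 changes. The first sequence holds the two parental variables (family activity and support). For the next three the text reads "change in children’s attitudes, subjective norms and perceived behavioral control between T0 and T3 will constitute the second sequence of mediators". The last sequence holds the children's scores for intentions, opportunities and planning, again as changes.
- Covariates: the linear models are run "whilst accounting for covariates (e.g.*,* age, sex, PA level at T0". The list is introduced as examples. PA is the only variable whose baseline value appears in it.
- Moderation: the effect of change in intentions on PA is tested across levels of planning and of perceived opportunities.

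The Evaluation section says that all variables are measured at T0, T1, T2 and T3, so every mediator's baseline score will be available. For the children's psychosocial variables, "Responses to all items are given using a four-point scale". The section on the theoretical framework says that "intentions are the proximal determinant of behavior".

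**The concern.** A raw change equals the T3 score minus the T0 score. Using it as regressor for a T3 level, without the T0 score in the model, forces the T0 score to have a coefficient equal and opposite to that of the T3 score. The trial's theory, which treats intentions as the immediate driver of behaviour, reads more naturally as a statement about current level. It gives no reason for a high starting score to count against later activity.

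The four-point items make this concrete. A child already at the top at T0 cannot improve, yet is expected to be active at T3, and enters as no change with high activity. A child rising from 1 to 3 enters as a large change but ends at a lower level. Both pull the fitted slope down.

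In linear models with common covariates and cases, the total effect is the direct effect plus the indirect effects. Whatever is lost from the indirect effects therefore reappears in the direct effect, and a mechanism that truly runs through the theory's variables could be reported as weak or absent.

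**Working it through.** The article gives no figure for the mediation analysis, so there is none to reproduce. It also gives no mediator stability, mediator–PA slope or PA stability. Those below are assumptions.

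**Simplest model.** Let X0 and X3 be a mediator at T0 and T3, each with variance 1 and correlation rx. Let PA at each time be P = b·X + u, with variance 1 and residual correlation ru between T0 and T3. Write Δ = X3 − X0.

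1. No baseline covariate: slope = Cov(P3, Δ)/Var(Δ) = b(1 − rx)/[2(1 − rx)] = b/2, whatever rx is.
2. With PA at T0, as the plan names: slope = [Cov(Δ,P3)·Var(P0) − Cov(Δ,P0)·Cov(P0,P3)] / [Var(Δ)·Var(P0) − Cov(Δ,P0)²].
   - Example with b = 0.3, rx = 0.5, ru = 0.3: Var(Δ) = 1; Cov(Δ,P3) = 0.3 × 0.5 = 0.15; Cov(Δ,P0) = −0.15; Cov(P0,P3) = 0.09 × 0.5 + 0.3 × 0.91 = 0.318.
   - Slope = (0.15 + 0.15 × 0.318)/(1 − 0.0225) = 0.1977/0.9775 = 0.202, or 0.67 of b.
   - Over b = 0.2, 0.3, 0.4, rx = 0.3, 0.5, 0.7 and ru = 0.3, 0.5, the ratio runs from 0.659 to 0.785.
3. With X0 added: ratio 1.000 in every cell of that grid.

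**Allowing a lagged effect of the T0 score.** Let P3 = b·X3 + d·X0 + error. Without baseline covariates the slope on Δ is (b − d)/2. Regressions on 1,000,000 simulated children per scenario (true b = 0.40, group-to-mediator effect 0.30, rx 0.3–0.7, T0 mediator–PA correlation 0.4), adjusted for PA at T0 but not for X0, gave:

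| d | fitted slope | indirect effect, share of truth |
|---|---|---|
| +0.2 | 0.13–0.14 | 0.33–0.36 |
| 0 | 0.22–0.23 | 0.55–0.57 |
| −0.2 | 0.31–0.32 | 0.77–0.79 |
| −0.4 (activity depends on the change) | 0.40 | 1.00 |

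With d = 0 and a T0 mediator–PA correlation from 0.2 to 0.8, the slope was 0.21 to 0.32. Adding X0 returned 0.40 throughout. The group-to-mediator path was 0.30 with or without X0, as randomisation implies.

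**Two mediators in sequence.** The truth was 0.40 from first to second, 0.40 from second to PA and 0 from first to PA. Raw changes gave 0.27–0.33, 0.18–0.27 and −0.03 to +0.01. Losses can thus compound along a sequence, and a single null path can move slightly off zero.

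**Where the T0-adjusted model is itself wrong** (truth 0.40):

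| Condition | without X0 | with X0 |
|---|---|---|
| stable unmeasured trait affecting mediator and PA | 0.29 | 0.57 |
| mediator reliability 0.6 | 0.10 | 0.22 |
| both | 0.12 | 0.32 |

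**The case against.** Four points can be made for the plan.

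- **The covariate list is only illustrative.** A reader might infer that the T0 scores are excluded. The text does not say so, and a full list may stand in a document not shown. This stands, and it is why the point is conditional. What the article does fix is raw-change mediators against a T3 level, and it names the baseline of PA but of no mediator. An analyst working from this text alone could well fit the attenuated model.
- **The section's stated purpose is to explain behavioural change by changes in the model's variables.** If activity truly depends on the change, the planned model has no bias. This also stands: a reader might infer that the indirect effects are always biased towards zero, and the last row of the lagged-effect table shows otherwise. Where d exceeds b, the formula without baseline covariates even reverses the sign.
- **Adjustment is not safe in itself.** Mediators are not randomised. With a stable unmeasured trait, the adjusted slope overshot by more (0.57 against 0.40) than the raw-change slope fell short (0.29). A reader might infer from the simplest model that adding T0 scores always restores the truth; that holds only without confounding or measurement error.
- **The size is not anchored.** It rests on assumed correlations, equal variances at T0 and T3, and mostly a single mediator. This stands.

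What survives is that including the T0 score estimates its coefficient instead of fixing it at minus the change coefficient. The planned model is then a special case of the wider one, and the change question can still be asked.

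**Conclusion.** The point holds as a conditional one. If the mediation models use only the named covariates, and T3 activity follows the mediator's T3 level, the mediator-to-PA paths and the indirect effects built on them are likely attenuated, to about 0.66–0.79 of the true value in the simplest model. Adjusting for PA at T0 repairs only part of the loss. A different assumed structure gave a larger loss (0.55–0.57), and dependence on the change itself gave none. All of these figures rest on correlations that the article does not supply.

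The group-to-mediator paths are not affected. Nor are the primary comparison and the intervention effects on the psychosocial scores, which come from separate mixed models. The consequence is confined to the secondary, explanatory question of whether the extended theory accounts for any effect. Because the remedy uses data already collected, it is worth making.

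**What to change.** In the mediation section, keep the change scores (or use the T3 scores; with T0 in the model the mediator's coefficient is the same) and state that each mediator's T0 score is a covariate in its own equation and in the PA equation, alongside PA at T0. Entering all eight T0 scores in every equation is the simplest way and also covers the mediator-to-mediator paths. In the moderation models, add T0 intentions, planning and perceived opportunities.

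Report the change-score model with only the named covariates as a sensitivity analysis. State that the adjusted paths remain open to measurement error and to unmeasured mediator–PA confounding, which can inflate them.

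The cost is a change of wording and up to eight more covariates, with no new data. That is negligible against the planned 4000 children. It is small in the parent subset too: if the pilot's 33.6% return for the parents' questionnaire applied to 4000, that would be 0.336 × 4000 = 1344 families before loss to follow-up. If the fuller plan already includes the T0 scores, saying so in this section closes the point.
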